### Safety measures

Surgeons operating on patients for this study have extensive experience with TEP repair (over 500 procedures per surgeon). Before the start of this study, every surgeon had performed over 20 procedures with an Ultrapro mesh, to prevent the occurrence of a ‘learning curve’ effect with a new mesh in the study period. Serious adverse events (SAE), other than SAEs that might eventually occur following endoscopic TEP repair (hemolytic shock, bladder or bowel injury) are not expected to occur in this trial.

### Sample size and power

The most common definition of chronic postoperative pain is from the International Association for the study of pain (IASP), where chronic pain is defined as pain lasting longer than three months following the primary operation, and other than the pain that was experienced preoperatively. The hypothesis is that the incidence of chronic pain is lower after implantation of a lightweight mesh (Ultrapro) than after implantation of a heavyweight mesh (Prolene). Based on a pilot study in our hosopital the assumption is made that 23% of the patients with a Prolene mesh will experience pain three months after TEP repair. In the Ultrapro group a reduction of 7.5% in the incidence of pain is expected. With a two-sided alpha of 0.05 and a power of 0.80, a total of 429 patients are to be included in each allocation group. Based on previous experience, a loss to follow-up of 10% is expected. Therefore, a total of 950 patients will be included in the TULP trial.

### Statistical methods

Data will be analyzed according to the intention-to-treat principle. SPSS software (SPSS, Chicago, IL, USA) will be used for statistical analysis. Descriptive statistics are used for baseline data. The incidence of the primary endpoint (moderate to severe chronic pain three months after endoscopic TEP repair as based on a NRS 4 to 10) will be compared between the Ultrapro and Prolene mesh group by means of Chi-square analysis. The comparisons of pain will be adjusted for analgesics used as a secondary supporting analysis. The number-needed-to-treat to prevent one case of chronic pain will be calculated. In an additional multiple logistic regression model, the effect of treatment on the primary endpoint will be assessed in relation to important risk factors for pain (younger age, severe pain in the postoperative period and severe preoperative pain [27]). Secondary endpoints will be analyzed by using a Student’s *t*-test (normally distributed continuous), Mann–Whitney analysis (not normally distributed continuous) or Chi-square analysis (categorical variables). The individual development of pain over time will be analyzed with repeated measurement strategies. Effect estimators are described with 95 % confidence intervals. Significance is set at a level of *p ≤ 0.05*.

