## Methods and design

### Study design

This is a prospective, double blind, randomized clinical trial involving a high-volume hospital in The Netherlands specialized in the TEP technique for inguinal hernia repair (Diakonessenhuis, Utrecht/Zeist, The Netherlands). All hernia operations are performed by four experienced TEP surgeons. Adult (≥18 years) male patients with primary, unilateral inguinal hernias, eligible for TEP hernia repair, are allocated to either lightweight mesh (Ultrapro, Ethicon, a Johnson & Johnson company, Amersfoort, The Netherlands) or heavyweight mesh (Prolene, Ethicon, a Johnson & Johnson company, Amersfoort, The Netherlands) by randomization. The total follow-up of patients is three years. A flowchart of the study with the estimated recruitment targets is shown in Figure 1. The design, conduct and reporting of this study will adhere to the Consolidated Standards of Reporting Trials (CONSORT) guidelines [16].

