### Intake

The study information is sent to patients after an appointment is made for an initial consultation. The appointment with one of four surgeons specialized in TEP hernia repair is scheduled within one week. After screening for eligibility criteria, informed consent is obtained and the patient is included in the study. Preoperative patient data are obtained by the coordinating investigator (Table 2).

**Table 2 T2:** Preoperative data

- Age	- Pain:^*^
- ASA-classification	· NRS score
- Co-morbidity (for example other pain syndromes)	· Brief Pain Inventory (BPI)
- Medication	· Inguinal Pain Questionnaire (IPQ)
- Smoking	· Carolinas Comfort Scale (CCS)
- Body Mass Index (BMI) - Education and occupation	· Pain-related Sexual Function Questionnaire (PSF)
- Health-related Quality of Life:^*^	
· SF-36 Questionnaire	
· EQ-5D Questionnaire	

* see section “Follow-up” of the manuscript (pages 7–8).

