### Follow-up

Several questionnaires are used for the assessment of pain and quality of life (also to evaluate which questionnaire can best be used to evaluate pain and its effect on quality of life in this patient population).

1) To assess the presence of postoperative pain, the following validated questionnaires are used:

Inguinal Pain Questionnaire (IPQ, Dutch version) [18]

Brief Pain Inventory, Short Form (BP-SF, Dutch version) [19,20]

Carolinas Comfort Scale (CCS, Dutch version) [21]

Numerical Rating Scale (NRS, 0 = no pain, 10 = extremely painful, Dutch version)

2) To measure the health related Quality of Life (QoL) the following validated questionnaires are used:

Short Form (36) Health Survey (SF-36, Dutch version) [22]

EuroQol 5D (EQ-5D, Dutch version) [23]

3) Finally, to assess the presence of pain related to sexual function, the PSF (pain related to sexual function) questionnaire is used, which is a Dutch translation of the questionnaire similar to the one previously described by Aasvang *et al.*[24] and based on the International Index of Erectile Function (IIEF) [25] to assess the presence, frequency, intensity and location of pain during sexual activity and the effect of pain on sexual function.

The patient is requested to record – on a daily basis during the first week immediately following surgery – the pain experienced, as well as the type and amount of analgesics used.

The NRS is used to assess the amount of experienced pain, where 0 = no pain and 10 = extremely painful. BPI and SF-36 questionnaires are filled in at Day 1 and Day 7 following surgery, to determine the effect of pain on daily activities.

After 6 weeks and 3, 12, 24 and 36 months, the IPQ, BPI, CCS, NRS, PSF, SF-36 and EQ-5D questionnaires are completed by the patients. To prevent bias, the questionnaires will be completed at home, or at the visit to the outpatient clinic at three months and one year postoperatively, in the absence of the surgeon or coordinating investigator, before the clinical assessment at the outpatient clinic. Patient satisfaction with the operative procedure is assessed at one week and three months after surgery on a 0 (= very unsatisfactory) to 10 (= very satisfactory) Likert scale.

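### The primary chi-square test and the SF-36, EQ-5D and PSF comparisons make no stated use of the preoperative values already collected: lost efficiency, not bias

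*Protocol article*

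**What the plan says.** **Main comparisons.** Under Statistical methods, the primary endpoint "will be compared between the Ultrapro and Prolene mesh group by means of Chi-square analysis". For the rest, "Secondary endpoints will be analyzed by using a Student" t-test if continuous and normal, and otherwise a Mann–Whitney "analysis (not normally distributed continuous) or Chi-square analysis (categorical variables"). No covariate is named for any of these tests.

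**Baseline data.** Under Intake, "Preoperative patient data are obtained by the coordinating investigator (Table 2"). Table 2 lists NRS, BPI, IPQ, CCS, PSF, SF-36 and EQ-5D, together with age. Under Follow-up, at 6 weeks and 3, 12, 24 and 36 months, "the IPQ, BPI, CCS, NRS, PSF, SF-36 and EQ-5D questionnaires are completed by the patients". Every one of these instruments therefore has a preoperative counterpart.

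**Where baseline does enter.** The same section adds: "In an additional multiple logistic regression model, the effect of treatment on the primary endpoint will be assessed in relation to important risk factors for". The factors that it then lists are "younger age, severe pain in the postoperative period and severe preoperative pain". This covers the primary endpoint only and supplements the chi-square test.

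**Pain over time.** The End-points section lists NRS, BPI, IPQ and CCS as measures of how pain develops, and Statistical methods assigns that question to repeated-measures methods. Whether the preoperative score enters them is not stated.

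**The concern.** The plan identifies two baseline predictors of its primary outcome, records both, and leaves them out of the test that decides the trial. Adjusting for a prognostic baseline value raises power at the same sample size and takes out chance imbalance in preoperative pain.

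The additional logistic model does not fill this gap. It includes severe pain in the postoperative period, which is measured after allocation. If the lighter mesh reduces early pain, holding early pain fixed removes part of the effect under test. The model therefore does not estimate the mesh effect adjusted for baseline alone, and no other stated analysis does.

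For SF-36, EQ-5D and PSF no baseline adjustment is stated at all, although quality of life is one of the two aims in the article's statement of purpose.

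**Working it through.** **Inputs from the protocol article (Sample size and power):** 23% with Prolene; a reduction of 7.5 points, so 15.5% with Ultrapro; two-sided alpha 0.05; power 0.80; 429 per arm; 10% loss; 950 in total.

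**Assumed inputs:** the strength of the link between preoperative score and outcome. The article gives none, so ranges are shown.

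**Step 1: the plan's own figure.** Unadjusted two-proportion formula, unpooled variance:

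n = (1.960 + 0.842)² × (0.23×0.77 + 0.155×0.845) / 0.075² = 429.9 per arm.

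The pooled version gives 433. The planned 429 is thus an unadjusted calculation and agrees with the unadjusted test.

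**Step 2: primary endpoint.** Evaluable patients: 950 × 0.9 = 855, about 428 per arm.

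- Unadjusted SE = √[(0.1771 + 0.1310)/428] = 0.0268. Power = Φ(0.075/0.0268 − 1.960) = 79.8%.
- Adjusted: let p₁(x) and p₂(x) be the risks in the two arms at standardised preoperative score x, from a logistic model calibrated to average 23% and 15.5%. Per-arm variance of the standardised risk difference: E[p₁(1−p₁)] + E[p₂(1−p₂)] + Var(p₁−p₂)/2. Its ratio to the unadjusted variance is the variance factor f. Power = Φ(0.075/(0.0268√f) − 1.960).

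| Assumed OR per SD | Variance factor | Power, unadjusted → adjusted |
|---|---|---|
| 1.5 | 0.975 | 79.8% → 80.8% |
| 2.0 | 0.932 | 79.8% → 82.5% |
| 2.5 | 0.888 | 79.8% → 84.3% |

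**Step 3: if the endpoint is rarer.** Same formulas, 428 per arm, about the same relative effect, OR 2 per SD (illustrative rates, not from the article):

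| Rates | Variance factor | Power, unadjusted → adjusted |
|---|---|---|
| 10% vs 6.7% | 0.961 | 41.6% → 43.0% |
| 5% vs 3.4% | 0.978 | 21.4% → 21.8% |

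The gain shrinks as events become rarer.

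**Step 4: continuous scores.** With baseline–follow-up correlation r, ANCOVA multiplies the variance by 1 − r². The 855 evaluable patients then carry the information of 855/(1 − r²). For an effect with 80% unadjusted power, adjusted power is Φ(2.802/√(1−r²) − 1.960).

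| Assumed r | Variance factor | Equivalent patients | Power |
|---|---|---|---|
| 0.3 | 0.91 | 940 | 83.6% |
| 0.4 | 0.84 | 1,018 | 86.4% |
| 0.5 | 0.75 | 1,140 | 89.9% |

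**The case against.** The strongest reply is that nothing here is wrong. An unadjusted chi-square test is valid under randomisation and matches the sample size calculation, as Step 1 shows. **This stands**, and it limits the point to efficiency.

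A second reply is that the gain is assumed. Chronic pain is defined in the article as pain different from that before surgery, so a strong link with preoperative NRS is not assured; at an OR of 1.5 the primary gain is about one power point. **This stands too.** The article's own naming of preoperative pain as a risk factor makes some link plausible but does not fix its size.

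A third reply is that adjustment is already planned through the additional logistic model. **This fails**, because that model also conditions on postoperative pain.

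Several stronger readings are tempting, and the article does not support them:

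- *All continuous secondary endpoints ignore baseline.* NRS, BPI, IPQ and CCS over time go to repeated-measures methods. Their covariates may be set in a fuller document that is not shown.
- *The Mann–Whitney test contradicts the promised confidence intervals.* A Hodges–Lehmann shift with a 95% interval can accompany it.
- *Adjustment matters more if the endpoint is rarer than planned.* Step 3 shows the reverse.
- *Surgeon must be in the model.* The article says "All hernia operations are performed by four experienced TEP surgeons", but it describes block randomisation without surgeon strata and does not call surgeon prognostic.

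**Conclusion.** The point holds as a loss of efficiency. The primary test and the SF-36, EQ-5D and PSF comparisons make no stated use of preoperative values that the trial records, and the only model that uses age and preoperative pain includes a post-randomisation covariate.

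The primary gain is about 1 to 4.5 power points for an assumed OR of 1.5–2.5 per SD at the planned rates, and less at lower rates. For continuous scores the variance falls by 9–25% for an assumed r of 0.3–0.5. These sizes rest on the assumed associations.

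A reader might infer that the planned results would be biased or the sample size wrong; neither follows. Endpoints with no preoperative score, such as hospital stay, complications, recurrence, return to work and satisfaction, are unaffected. The change is worth making because it costs almost nothing, not because the trial fails without it.

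**What to change.** 1. **Primary endpoint.** Prespecify a logistic model of NRS 4–10 at three months on mesh, preoperative NRS and age, both continuous, without postoperative pain. Report the standardised risk difference with its 95% CI and derive the number needed to treat from it. This keeps the chi-square test's target, a difference in risk between the arms. Retain the chi-square test as a sensitivity analysis.
2. **SF-36, EQ-5D and continuous PSF scores.** Use ANCOVA or a mixed model with the preoperative score as covariate.
3. **NRS, BPI, IPQ and CCS over time.** State that the preoperative score enters the planned repeated-measures models.
4. **Postoperative pain.** If the model containing it is kept, label it exploratory and do not read its mesh coefficient as the treatment effect.

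Surgeon may be added but need not be. The cost is analysis wording, plus a stated rule for patients who lack a preoperative score. No new data, visits or patients are needed. Fix the wording before allocation is unblinded for analysis.

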### Randomization

Patients are randomly assigned to either Ultrapro or Prolene mesh in the operating room (after patients are under general anesthesia) by computerized block randomization. Follow-up of patients will take place according to the intention-to-treat principle. The patient, coordinating investigator and the surgeon involved in the follow-up of enrolled patients are blinded for the allocated mesh. Obviously, the operating surgeon cannot be blinded to the study because of the characteristic composition of the two meshes. To avoid bias, the mesh type is not mentioned in the operating chart. In addition, the follow-up is not by the operating surgeon, but by one of the other three surgeons specialized in hernia repair.

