### Postoperative management

Patients are discharged on the day of surgery, unless complications occur. The duration of hospital stay and postoperative complications are registered in the EPD. At discharge, patients are advised to take analgesics (Paracetamol and, if necessary, Diclofenac), when necessary and avoid strenuous physical activity (lifting, sports) during the first post-operative week. There are no other (physical) restrictions. The type and amount of analgesics used during the first postoperative week are kept in a pain diary.

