All patients are examined in the outpatient department by one of the four surgeons (different from the operating surgeon) and the coordinating investigator at three months and one year after surgery. The physical examination is, if necessary, supplemented with an Ultrasound or MRI scan in patients with groin pain and/or complaints suggestive of a recurrent hernia.

All visits include standardized clinical evaluation (according to the validated ‘Inguinal Pain Form (Dutch ‘Liespijnformulier’) by Loos [26]) and registration of possible complications. Parameters assessed at the outpatient evaluation are:

Complications after surgery

Short term (for example: seroma, hematoma, wound-infection, urinary retention, constipation)

Long term (for example: testicular atrophy, mesh infection)

The presence of a recurrent hernia

The presence of a contra-lateral hernia

Other non-hernia related problems in the groin region (for example, hydrocele, varicocele, prostate problems/hidradenitis)

Postoperative pain

Characteristics of pain

The relation of pain to daily activities, physical activity and/or sexual activity

Possible treatment of pain

Mesh feeling

Sensibility disorders in the inguinal/scrotal/thigh/umbilical region or elsewhere

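### Adjusting the pain comparisons for analgesics used conditions on a consequence of pain, so the adjusted result is not the total mesh effect and may be biased in either direction

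*Protocol article*

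**What the plan says.** The Statistical methods section compares the primary endpoint, NRS 4-10 at three months, by an unadjusted Chi-square test under intention to treat. It then adds: "The comparisons of pain will be adjusted for analgesics used as a secondary supporting analysis". It names neither the analgesic variable nor the time points of the pain comparisons to be adjusted.

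Four other places in the protocol article show what this variable can be.

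- Randomization: allocation takes place "in the operating room (after patients are under general anesthesia) by computerized block randomization", so every postoperative analgesic comes after it.
- Postoperative management: at discharge "patients are advised to take analgesics (Paracetamol and, if necessary, Diclofenac), when necessary". The same section says: "The type and amount of analgesics used during the first postoperative week are kept in a pain diary".
- Follow-up, first week: "on a daily basis during the first week immediately following surgery" the patient records "the pain experienced, as well as the type and amount of analgesics used".
- Follow-up, later: "After 6 weeks and 3, 12, 24 and 36 months, the IPQ, BPI, CCS, NRS, PSF, SF-36 and EQ-5D questionnaires are completed by the patients". No analgesic diary is among these instruments. The clinic visits at three months and one year list "Possible treatment of pain", without type or amount.

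Medication is also recorded preoperatively (Table 2).

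**The concern.** A patient who hurts more takes more analgesics. A model that holds analgesic use fixed compares the two meshes among patients with similar analgesic need. If the mesh changes early pain, and early pain is related to later pain, the model removes part of the effect that the trial sets out to measure. Unmeasured susceptibility to pain, which drives both analgesic use and chronic pain, can add further distortion once use is held fixed.

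The timing is a second difficulty. The only analgesic record with type and amount covers the first week, while the primary endpoint is at three months. A first-week measure carries no information on whether a three-month NRS was lowered by drugs taken at three months.

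At stake is the reading of the primary result. The adjusted analysis is meant to support it, but could appear to weaken or strengthen it for reasons unrelated to what the mesh does.

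**Working it through.** **The plan's own figure.** No figure is given for the adjusted analysis. The sample-size inputs set the scale: 23% on Prolene and, reading the 7.5% reduction as absolute, 15.5% on Ultrapro. With unpooled variance, n = (1.960 + 0.842)² × (0.23×0.77 + 0.155×0.845) / 0.075² = 7.849 × 0.3081 / 0.005625 ≈ 430 per group, against 429 stated. The design effect is thus a risk difference of -0.075, or an odds ratio of (0.155/0.845)/(0.23/0.77) = 0.61. The present point changes none of this.

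**A hand calculation.** Assumptions: 30% of Prolene patients need analgesics in week 1; the lighter mesh has odds ratio 0.5 on that need; need has odds ratio 4 on three-month pain. Only the 23% comes from the documents.

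1. Need on Ultrapro: odds 0.30/0.70 × 0.5 = 0.214, so 17.65%.
2. Three-month pain on Prolene is 0.1507 without need and 0.4151 with need. Check: 0.70×0.1507 + 0.30×0.4151 = 0.230.
3. No direct mesh effect: Ultrapro risk = 0.8235×0.1507 + 0.1765×0.4151 = 0.197. Crude odds ratio (0.197/0.803)/(0.23/0.77) = 0.82; adjusted odds ratio 1.00. The real difference of -0.033 disappears.
4. Direct odds ratio 0.80: Ultrapro risks 0.1243 and 0.3621, total 0.8235×0.1243 + 0.1765×0.3621 = 0.166. Crude odds ratio 0.67; adjusted 0.80.

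With need of 40-60% on Prolene, the crude odds ratios in steps 3 and 4 are about 0.80 and 0.65. With a weaker mesh effect on need (odds ratio 0.7) they are 0.89-0.90 and 0.72-0.73. The adjusted values stay at 1.00 and 0.80.

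**Both directions.** Odds ratios move a little under adjustment even without bias, so the wider check uses risk differences. Each scenario simulates 400,000 patients. In the first-week scenarios:

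- early pain = a·mesh + 0.7·u + normal noise, where u is shared susceptibility to pain;
- the logit of analgesic use = -0.3 + g·early pain;
- latent three-month pain = d·mesh + b·early pain + 0.7·u + logistic noise, cut so that 23% of Prolene patients are cases.

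The adjusted figure is the risk difference standardized from a logistic model with mesh and analgesic use.

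| Week-1 use as covariate | a, b, g, d | Use, Prolene / Ultrapro | Crude | Adjusted |
|---|---|---|---|---|
| Lighter mesh lowers early pain | -0.5, 0.6, 1, -0.25 | 0.44 / 0.35 | -0.069 | -0.056 |
| Same, use tied more closely to pain | -0.5, 0.6, 2, -0.25 | 0.46 / 0.33 | -0.070 | -0.044 |
| Whole effect through early pain | -1, 1, 2, 0 | 0.46 / 0.22 | -0.102 | -0.042 |
| No mesh effect on early pain | 0, 0.6, 1, -0.55 | 0.44 / 0.44 | -0.069 | -0.069 |
| Lighter mesh raises early pain | 0.5, 0.6, 1, -0.8 | 0.44 / 0.54 | -0.061 | -0.075 |

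If use at three months were the covariate instead (use 0.19 / 0.14), the crude difference moves from -0.078 to -0.059 when the drug does not lower the score. It moves from -0.065 to -0.073 when the drug masks pain very strongly. A covariate measured at the right time therefore does not cure the problem. Repeating these scenarios with other random numbers moved each figure by at most 0.003.

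**The case against.** A reader might infer that the adjustment must bias the result toward no difference. The documents do not support that. It requires the lighter mesh to lower early pain or analgesic use, and the stated hypothesis concerns chronic pain only. With no early effect, adjusting for week-1 use does no harm; with higher early use the shift is away from no difference. This part of the objection stands.

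A reader might also infer that the three-month comparison will certainly be adjusted for the week-1 diary, or that no later analgesic data exist. Neither is established. The variable is not named, the three-month visit lists a pain-treatment item, and the item content of the questionnaires is not shown. For first-week pain the diary is contemporaneous. So the timing objection applies only if the diary is the covariate. The objection to the covariate itself does not depend on timing, because analgesic use at any postoperative time is driven by pain.

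It can be said that if the three-month treatment item is good enough for a composite endpoint, it is good enough as a covariate. That does not follow. As part of the outcome, it counts a treated patient as a case. As a covariate, it holds fixed a consequence of the outcome.

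The exact covariate and time point could be left to a fuller document. Choosing postoperative analgesic use as an adjustment variable, however, is already stated here. Preoperative medication would be a legitimate covariate, but the wording matches the postoperative diary rather than Table 2.

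Finally, the analysis is labelled secondary and supportive, and no decision depends on it. That stands and limits the weight of the point.

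**Conclusion.** The point holds in a limited form. Adjusting pain comparisons for postoperative analgesic use does not estimate the total, intention-to-treat effect of mesh. If the first-week diary supplies the covariate, it also cannot correct the three-month NRS for analgesics taken then.

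The bias may be nil or may go either way. Across the assumed first-week scenarios, the adjusted risk difference ranged from about 40% of the crude one (-0.042/-0.102 = 0.41) to about 120% of it (-0.075/-0.061 = 1.23). All path strengths are assumptions; only the 23% control rate comes from the protocol. These figures show what can happen and do not predict this trial.

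The primary Chi-square test, the number needed to treat derived from that comparison and the sample size are untouched. The change should be made because an adjustment with bias of unknown size and sign gives no dependable support to the primary result.

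**What to change.** Remove analgesic use as a covariate from the pain comparisons, and restrict any adjustment of the mesh effect to variables measured before randomization. Report first-week analgesic use by arm as an outcome in its own right, from the diary already planned. If masking at three months is a concern, add a supportive endpoint of NRS 4-10 or current treatment for groin pain, compared by arm, with a consistent yes/no coding of the treatment item already listed for the three-month visit.

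The cost is a change of wording and some coding work. The composite mixes pain with treatment use, so it should be shown beside the NRS result and not replace it. Visits, sample size and the primary test stay as they are.

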### End-points

The primary endpoint is the presence of moderate to severe chronic pain three months after an endoscopic preperitoneal (TEP) hernia correction, as measured by the NRS. The definition of the International Association for the Study of PAIN (IASP) is used with chronic postoperative pain being defined as pain still present at the site of the operation three months after the primary surgery and different from the pain before the operation. Pain is measured on a 0 (= no pain) to 10 (extremely painful) scale. In accordance with the literature, the following cut-off values for pain are used: [26]

Mild pain: NRS 1 to 3

Moderate pain: NRS 4 to 6

Severe pain: NRS 7 to 10

Moderate to severe pain is considered as clinically relevant [26]. Only moderate to severe pain (NRS 4 to 10) will, therefore, represent ‘chronic pain’ in this study. Secondary endpoints are:

Duration of hospital stay

Complications: intra-operative, post-operative period (until three months after surgery), long-term (until three years after surgery, for example, testicular atrophy)

Time to resume daily activities and return to work

Recurrent hernia

Contra-lateral hernia

Development of pain over time as measured by the NRS score at the first week following TEP repair and 6 weeks, 12, 24 and 36 months postoperatively

Development of pain over time as measured by the BPI, IPQ and CCS questionnaires: the presence of pain in the first week postoperatively and after 6 weeks, 3 months, 12, 24 and 36 months

Development of pain, sensitivity disorders (anesthesia, hypoesthesia, hyperesthesia, allodynia) and or discomfort (including sensation of ‘mesh presence’ at the outpatient visit at three months and one year post-operatively

Health related quality of life as measured by the SF-36 and EQ-5D questionnaires

Pain related sexual function as measured by the PSF questionnaire

Patient satisfaction with the procedure and perioperative care

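### The additional logistic regression for the mesh effect adjusts for postoperative pain, a post-randomisation outcome; if the mesh affects early pain, the adjusted odds ratio no longer estimates the total randomised effect

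*Protocol article*

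**What the plan says.** All references are to the protocol article.

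- **Primary analysis** (Statistical methods): the incidence of moderate to severe pain at three months "will be compared between the Ultrapro and Prolene mesh group by means of Chi-square analysis". This comparison is unadjusted.
- **Regression** (Statistical methods): "In an additional multiple logistic regression model, the effect of treatment on the primary endpoint will be assessed in relation to important risk factors". The factors listed are "important risk factors for pain (younger age, severe pain in the postoperative period and severe preoperative pain".
- **Timing** (Randomization): patients are allocated "in the operating room (after patients are under general anesthesia) by computerized block randomization", so any postoperative pain follows allocation.
- **Measurement** (Follow-up): patients record their pain "on a daily basis during the first week immediately following surgery".
- **Role as an outcome** (End-points): a secondary endpoint is "Development of pain over time as measured by the NRS score at the first week following TEP repair and 6 weeks", with later time points following.
- **Hypothesis** (Sample size and power): that "the incidence of chronic pain is lower after implantation of a lightweight mesh (Ultrapro) than after implantation of a heavyweight mesh (Prolene". It concerns chronic pain only.

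The article does not describe the regression as purely prognostic or as a mediation analysis, and it does not limit the covariates to baseline variables.

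**The concern.** The stated purpose of the regression is to assess the treatment effect. Two of its three covariates, age and preoperative pain, are fixed before the mesh is implanted. The third is not. Postoperative pain is observed after allocation, will be compared between the arms as an outcome, and is named by the plan as a risk factor for the primary endpoint. It may therefore lie on the path from mesh to chronic pain.

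If it does, conditioning on it has two consequences. It takes out the part of the mesh effect that acts through early pain. It can also link mesh type to unmeasured pain susceptibility within levels of early pain, which undoes the protection of randomisation for that estimate.

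What is at stake is the reading of the trial's adjusted result. The hypothesis is a benefit of the lightweight mesh. If that mesh lowers both early and chronic pain, adjustment pulls the OR towards 1. The chi-square test and the regression could then appear to disagree, although they answer different questions.

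**Working it through.** **1. The plan's own figure.** Inputs from Sample size and power: 23% on Prolene, a reduction of 7.5 points to 15.5%, two-sided alpha 0.05, power 0.80. The unpooled formula is

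n = (z₀.₉₇₅ + z₀.₈₀)² × [p₁(1−p₁) + p₂(1−p₂)] / (p₁−p₂)²
= (1.960 + 0.842)² × (0.1771 + 0.1310) / 0.075² = 429.9 per arm.

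The plan states 429; the pooled-variance version gives 433. With 10% loss, 858/0.90 is about 954, against the stated 950. The plan's figure reproduces. None of these inputs involves the covariate, so removing it leaves the sample size unchanged. The planned total effect as an OR is (0.155/0.845)/(0.23/0.77) = 0.614.

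**2. Model for the illustration.** The article gives neither a rate of severe early pain nor its link to chronic pain. Assumed: severe early pain in 30% on Prolene and OR 4 from early to chronic pain. The 23% chronic-pain rate on Prolene comes from the plan. Solving 0.30 × r₁ + 0.70 × r₀ = 0.23 with odds(r₁) = 4 × odds(r₀) gives chronic-pain risks on Prolene of r₀ = 0.151 without and r₁ = 0.415 with severe early pain.

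For Ultrapro, let m be the early-pain rate implied by the mesh OR on early pain. The direct mesh OR multiplies the odds of r₀ and r₁ to give s₀ and s₁. The chronic-pain risk is m × s₁ + (1−m) × s₀. The total OR compares the odds of that risk with 0.23/0.77. With no unmeasured common cause, the adjusted OR equals the direct OR.

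**3. Direct mesh OR 0.8** (s₀ = 0.124, s₁ = 0.362):

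| Mesh OR on early pain | Early pain, Ultrapro | Chronic pain, Ultrapro | Total OR | Adjusted OR |
|---|---|---|---|---|
| 0.5 | 17.6% | 16.6% | 0.67 | 0.80 |
| 0.8 | 25.5% | 18.5% | 0.76 | 0.80 |
| 0.9 | 27.8% | 19.1% | 0.79 | 0.80 |

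First row worked: 0.1765 × 0.3621 + 0.8235 × 0.1243 = 0.166; (0.166/0.834)/(0.23/0.77) = 0.67.

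**4. No direct effect** (s₀ = r₀, s₁ = r₁):

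| Mesh OR on early pain | Chronic pain, Ultrapro | Total OR | Adjusted OR |
|---|---|---|---|
| 0.5 | 19.7% | 0.82 | 1.00 |
| 0.8 | 21.8% | 0.93 | 1.00 |
| 0.9 | 22.4% | 0.97 | 1.00 |

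Here the whole mesh effect runs through early pain, and adjustment removes all of it.

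**5. At the planned effect.** Hold the marginal risks at 23% and 15.5% (total OR 0.614) and early pain on Prolene at 30%. Let the OR from early to chronic pain be 3 to 5, with or without a binary unmeasured common cause (50% prevalence, OR 3 on each pain). The adjusted OR is:

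- 0.64 if early pain on Ultrapro is 25%
- 0.68 to 0.73 if it is 20%
- 0.73 to 0.83 if it is 15%
- 0.57 to 0.60 if it is 30%, so that the mesh has no effect on early pain

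Without a common cause, the last shift is non-collapsibility of the OR alone and not mediation. With the common cause, the adjusted OR also departs from the direct OR. For example, at 15% early pain and OR 3 it is 0.76 against a direct OR of 0.72, so it estimates neither the total nor the direct effect cleanly.

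**The case against.** The strongest defence has four parts.

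**The model is only additional.** This stands. The chi-square test carries the primary comparison, and no sentence lets the regression supersede it. A reader might infer that the trial's main conclusion is compromised; the article does not support that.

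**Bias requires that the mesh changes early pain.** This also stands. Listing first-week pain as an endpoint means that it will be compared, not that a difference is expected. The article says that the absorbable part of Ultrapro takes 90 to 120 days to disappear, so in the first week that mesh has not reached its final form and a large early difference is not an obvious premise. A reader might infer that the adjusted effect is certainly biased; the documents support only a conditional statement. The choice of covariates should nevertheless not depend on an unknown that the trial itself will measure.

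**A large gap needs a strong assumption.** This is fair. A mesh OR of 0.5 on early pain means a fall from 30% to 17.6%, about 12 points, which exceeds the 7.5 points planned for the primary endpoint. At OR 0.8 or 0.9 the gap is small. A reader might also infer that adjustment would turn a benefit into an apparent harm. With no direct effect, a mesh OR of 0.5 on early pain and a binary common cause (50% prevalence, OR 3 to 5 on both pains), the adjusted OR is only 1.03 to 1.06. That needs a strong early effect and a strong hidden cause together, and the article gives evidence of neither.

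**Assessing the effect in relation to risk factors could mean interaction, or the analysis plan may settle it.** This does not stand. An interaction with postoperative pain also conditions on a post-randomisation variable. The point is also not a missing detail, because the article itself names the covariate.

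**Conclusion.** The concern holds in conditional form. The plan places a post-randomisation variable that is itself a trial outcome in a model meant to assess the mesh effect. If the mesh affects early pain, the resulting OR does not estimate the total randomised effect.

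Under the stated assumptions, the gap between total and adjusted OR runs from 0.79 against 0.80 to 0.67 against 0.80 with a direct OR of 0.8. With no direct effect it runs from 0.97 against 1.00 to 0.82 against 1.00. The early-pain rate, its link to chronic pain and the mesh effect on it are all assumed, so the true size cannot be derived from the article. Severity is moderate: a supporting analysis is misspecified, while the primary test, the number-needed-to-treat and the sample size are untouched.

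**What to change.** In Statistical methods, restrict the covariates of the treatment-effect regression to those fixed before implantation, namely age and preoperative pain, and delete severe postoperative pain from that model. If its role is of interest, report it in a separate analysis labelled as prognostic or mediational, which makes no claim about the total mesh effect.

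The cost is one or two sentences of analysis wording. No new data are needed, and the planned 429 per arm and 950 in total do not change.
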